### Definitions

3.7

•**Current cigarette smoker:** Average of ≥5 cigarettes daily use in at least the year before enrollment.•**Successful smoking cessation:** Continuous abstinence in at least 4 weeks during 6 months following up.•**Uncontrolled DLP:** Description for uncontrolled DLP will be based on the serum level of LDL-C which depends on the concomitant comorbidities including diabetes mellitus and CVD [18]. The related cut-off value for the serum level of target LDL-C is ≤ 55 mg/dL. Values more than the listed cut-off value are considered uncontrolled DLP.•**Controlled DLP**: Lowering serum level of LDL-C by < 55 mg/dL and ≥50% reduction from baseline in any of the follow-up visits at the end of 3 and 6 months from randomization and remaining controlled in the next visits during the study.•**Uncontrolled HTN:** A patient who has a history of HTN with/without using the antihypertensive drug is considered hypertensive. Participants will be considered as having uncontrolled HTN according to the ACC/AHA guidelines [19].•**Controlled HTN:** Maintaining BP below the target treatment level (130/80 mmHg) at the time of office measurements (average of 2 readings obtained on 2 separate occasions with proper patient preparation and appropriate technique) at the end of 3 and 6 months from randomization and/or during one-week daily home measurements (average of records) before clinic visits.

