### Study outcomes

3.6

**Primary outcome:** Successful risk factors’ control measured at 3 and 6 months after randomization.

This outcome will be categorical as follows.1No controlled risk factors2One controlled risk factor3Two controlled risk factors4Three controlled risk factors

**Secondary outcomes**: Includes risk factors control in each level of stratification (7 levels presented early in the method section).1Number of participants who remain active users of the app till to the end of the intervention.2Controlled CS3Controlled HTN4Controlled DLP5Controlled CS + HTN6Controlled CS + DLP7Controlled HTN + DLP8Controlled HTN + DLP + CS

The definition of being controlled for each risk factor is presented in the “Definitions” section. Each risk factor that meets the outcome will be regarded as a successful intervention.

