### Participants

3.8

According to eligibility criteria (Table 1), 1544 individuals will be selected. Participants in both arms will receive their routine care and the intervention arm will be encouraged to follow guides for each risk factor using the app in addition to the routine care. After 3 and 6 months, the status of risk factors will be determined through outpatient visits and face-to-face interviews for both arms. All the participants will be visited in an outpatient clinic by a cardiologist to evaluate the status of the risk factors and document any cardiovascular events (outcomes). Any additional visits will be considered for any patient requiring fewer interval visits.

During study time, patients in the intervention arm will be encouraged to continue to use the app. The patients in both arms will be allowed to have their routine care inside and outside THC whenever needed. The participant timeline and summary of the study protocol are summarized in Table 2 and Fig. 1, respectively.

**Table 2 tbl2:** Participant timeline.

		Study period			
		Enrollment	Allocation	Post-allocation	Close-out
**Month**		−3 ± 2 days	0	3	6
**Enrollment**		×			
**Eligibility screen**		×			
**Informed consent**		×			
**Allocation**			×		
**Intervention**			×	×	×
**Assessment**	Baseline variables	×		×	×
	Measuring systolic and diastolic blood pressure	×		×	×
	Evaluating smoking status	×		×	×
	Measuring low-density lipoprotein cholesterol serum level	×		×	×
	Evaluating adherence to treatment and diet			×	×
	Evaluating the usability (data entry) and satisfaction level of software/application			×	×

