### Statistical methods

3.12

Continuous variables will be presented through mean with the standard deviation (SD) for normally distributed variables or median with the interquartile range boundaries for skewed variables. Categorical variables will be presented as the frequency with percentage. To check the normality distribution of continuous variables, histograms will be applied along with the above descriptive quantities. Risk factors’ status will be measured at different time points to determine the final status at the end of certain time points. We will compare the prevalence of the controlled risk factors in time points of 0 (baseline), 3 and 6 months between intervention and control groups using x^2^ tests at each point. Multivariate logistic regression analysis will be used to determine the effect of the intervention on the control of risk factors at the end of 6 months. The effect will be reported as Odds Ratios with the corresponding 95% confidence interval. This will be a per-protocol approach. To perform the intention-to-treat method, participants will be analyzed according to the group they were allocated not the actual intervention they received. The missing values for subjects who were lost to follow-up or did not cooperate until the end of the study will be evaluated to see to what extent the missing data are completely random. If missing data do not violate the randomness assumption, they will be replaced using the multivariate missing imputation method. Otherwise, stratified analysis and sensitivity analysis for missing data will be considered. Finally, the size of the effect is measured and reported as a relative risk/risk ratio with a corresponding 95% confidence interval. The effect will be calculated and reported as a hazard ratio with the corresponding confidence interval.

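### Smoking control is met by any 4-week abstinent spell in 6 months, with no visit anchor or relapse condition, so a patient smoking at the 6-month visit can count as controlled

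*Protocol article*

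**What the plan says.** All places are in the protocol article.

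- **Study outcomes (3.6).** The primary outcome is "Successful risk factors’ control measured at 3 and 6 months after randomization", scored as the number of controlled risk factors from none to three. For what counts as controlled, the section refers elsewhere: "The definition of being controlled for each risk factor is presented in the “Definitions” section".
- **Definitions (3.7), smoking.** The only rule for success is "Continuous abstinence in at least 4 weeks during 6 months following up".
- **Definitions (3.7), dyslipidemia.** The LDL-C target must be reached at a follow-up visit, with the patient then "remaining controlled in the next visits during the study".
- **Definitions (3.7), hypertension.** Blood pressure must be below target at office measurements "at the end of 3 and 6 months from randomization and/or during one-week daily home measurements (average of records) before clinic visits".
- **Participants (3.8).** "After 3 and 6 months, the status of risk factors will be determined through outpatient visits and face-to-face interviews for both arms". Table 2 lists an evaluation of smoking status at both months.
- **Statistical methods (3.12).** "We will compare the prevalence of the controlled risk factors in time points of 0 (baseline), 3 and 6 months between intervention and control groups". A logistic model then estimates "the effect of the intervention on the control of risk factors at the end of 6 months".
- **Sample size calculation (3.9).** Smoking, at 8% versus 12%, sets the size of the trial: 772 per arm, 1544 in total.

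**The concern.** The outcome and the analysis describe a state: is the risk factor controlled at this visit? The smoking rule describes an event: did a 4-week abstinent spell occur at some time during follow-up? Once that event has happened, the rule as written cannot be undone by later smoking. The primary count then adds two components tied to the visits to one that is not.

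The stakes are higher than for a minor component. Smoking sets the sample size, is one of the three risk factors counted, and enters four of the eight secondary outcomes (smoking alone, both smoking pairs, and all three together). The app's smoking module has a quit-plan builder, automated messages and push notifications, so it could plausibly produce more quit attempts, some of them short. Under the written rule each attempt that lasts 4 weeks counts in full, whatever follows.

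**Working it through.** **1. What the rule admits.** Six months is about 26 weeks. Four weeks is 4/26 = 15% of follow-up. A patient abstinent in weeks 2 to 5 and smoking in the other 22 weeks or so, including at the 6-month visit, meets the rule.

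**2. The three components side by side.**

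| Component | Tied to the visits? | Lost on relapse? |
|---|---|---|
| Dyslipidemia | Yes, LDL-C at the 3- and 6-month visits | Yes, must remain controlled |
| Hypertension | Yes, office readings at 3 and 6 months and/or home readings in the week before | No explicit clause, but judged at or just before each visit |
| Smoking | No, any time in 6 months | No |

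Only the smoking rule lets a success that has already been lost count at month 6.

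**3. What can be scored at 3 months.** Four weeks fit inside 3 months, so a spell completed by then can be identified. What is missing is a 3-month window for a patient without such a spell, and a statement on whether an early success carries forward to month 6.

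**4. Reproducing the planned size.** Inputs from section 3.9 and Table 3: p1 = 0.08, p2 = 0.12, alpha 0.05, power 80%, loss 10%.

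n = [z_a √(2p̄(1−p̄)) + z_b √(p1(1−p1) + p2(1−p2))]² / (p2−p1)², with p̄ = 0.10.

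One-sided: (1.6449 × 0.4243 + 0.8416 × 0.4233)² / 0.04² = 694.5, and 694.5 / 0.9 = 771.7, rounded up to the stated 772. A two-sided alpha gives 882, or 980 after loss, which does not match. The protocol does not state sidedness. That is a separate matter; one-sided is used below only to stay on the plan's own scale.

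**5. Same relapse share in both arms.** Assume that the 8% and 12% are any-spell rates, and that a share r of these quitters has relapsed by month 6. Abstinent at month 6: 0.08(1−r) and 0.12(1−r). Power uses the 694 per arm left after 10% loss (772 × 0.9 = 694.8, rounded down):

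power = Φ{[(p2−p1)√694 − 1.6449 √(2p̄(1−p̄))] / √(p1(1−p1) + p2(1−p2))}.

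| r (assumed) | Control | App | Risk ratio | n per arm before loss | Power at 694 |
|---|---|---|---|---|---|
| 0 | 8% | 12% | 1.5 | 695 | 80% |
| 25% | 6% | 9% | 1.5 | 953 | 68% |
| 50% | 4% | 6% | 1.5 | 1468 | 53% |

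For r = 25%: (0.03 × 26.34 − 1.6449 × 0.3725) / 0.3719 = 0.478, and Φ = 0.68. For r = 50%: (0.02 × 26.34 − 1.6449 × 0.3082) / 0.3079 = 0.065, and Φ = 0.53. Like the plan's own calculation, these figures treat every patient counted as a smoker.

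**6. More short-lived quits in the app arm.** Assume equal abstinence of 8% at month 6, plus relapsed spells in 4% to 6% of control and 8% to 10% of app patients. The written rule gives (0.08 + 0.08)/(0.08 + 0.04) = 1.33, or (0.08 + 0.10)/(0.08 + 0.06) = 1.29, where the ratio at month 6 is 0.08/0.08 = 1.0. These rates are invented for illustration. With the excess in the control arm instead, the error would run the other way.

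**The case against.** The strongest reply accepts the wording and disputes what is built on it. Three inferences that a reader might draw are not supported.

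- **Smoking cannot be scored at 3 months.** It can, for anyone who has completed 4 abstinent weeks by then, and Table 2 schedules the assessment. Only the window and the carry-forward rule are missing.
- **The rule is shown to favour the app.** It is not. The risk ratios of 1.29 to 1.33 rest wholly on an assumed excess of relapsed spells in the app arm. With the same relapse share in both arms the ratio does not move. The app's smoking forms are described as baseline and follow-up forms and its notifications without a frequency, so daily prompting cannot be read from the text. Nor are the app's forms named as the source of the outcome: status is determined at visits and interviews in both arms, by blinded practitioners.
- **Smoking is a third of every patient's count.** Three of the seven randomization strata contain no smokers. If the referral proportions in Table 3 carried over to trial patients, smoking would be about 0.34/(0.72 + 0.47 + 0.34) = 22% of the risk factors.

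Two further points also stand. A rule based on the 4 weeks before the visit is still self-report by patients who know their arm. It also does not prove sustained abstinence: someone who smoked for 22 weeks and stopped for the last four would count as controlled at month 6.

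None of this removes the central point, that a relapsed smoker is scored as controlled at a visit where he or she is smoking. Nor can it be left to a fuller document as omitted detail, because the article states the rule.

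**Conclusion.** The concern holds as a conflict between a stated outcome definition and the outcome and analysis that use it. It rests on the plain wording of the smoking definition and on the absence from the article of any other rule for smoking control. It needs correcting before outcome data are examined, because the two readings score the same patient differently on the primary outcome.

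The size and direction of any bias cannot be determined from the documents. Proportionally equal relapse leaves the risk ratio at 1.5 and lowers both absolute rates; an excess of short-lived quits in the app arm would overstate the effect. The power figures of 68% and 53% apply only if Table 3's rates are any-spell rates and the relapse share is 25% or 50%. The article does not say which definition those rates follow.

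**What to change.** 1. In Definitions, define smoking control separately at 3 and at 6 months as no cigarette in the 4 weeks immediately before that visit. Ask the same question in the same way in both arms. This settles the 3-month window, relapse and carry-forward together.
2. Report any 4-week abstinent spell during follow-up as a separate quit-attempt outcome, outside the primary count.
3. Confirm whether the 8% and 12% in Table 3 refer to the visit-based definition. If they do not, replace them and restate the power.

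The procedural cost is small: one definition and one question at visits where smoking status is already assessed. The statistical cost is that measured quit rates will be lower, and the stated power possibly lower too. The change aligns the outcome with the visits; it does not remove self-report or establish abstinence beyond the 4 weeks asked about.

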### Sample size calculation

3.9

Farkouh et al. [22] which studied pooled data obtained from large randomized trials display the success rate in controlling risk factors in CAD patients for secondary prevention through lifestyle modification and drug consumption.

To increase the success rate percentage of modifying the risk factors by at least 1.5 times, concerning significance level of α = 0.05, study power of 80% and 10% loss of samples, a sample size of 257, 538, and 772 were considered for DLP, HTN, and CS, respectively. The largest sample size of 772 which is related to CS was selected (772 × 2 = 1544). The calculation was performed by G-power software. The final results are reported in Table 3.

**Table 3 tbl3:** Success rates in controlling Dyslipidemia, Hypertension and smoking and calculated sample size.

Risk Factor	Success rate percentage in the control group	Success rate percentage in the intervention group	Sample size in each group counting 10% shedding of samples	The abundance of patients referred to the Tehran Heart Center
**Dyslipidemia**	0.2	0.3	257	0.72
**Hypertension**	0.11	0.165	538	0.47
**Cigarette smoking**	0.08	0.12	772	0.34

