### Randomization and implementation

3.10

Randomization will be performed at 7 different levels based on the type and number of risk factors the patients have (stratified randomization). Participants will be categorized into the following 7 levels; 1) Only CS, 2) Only HTN, 3) Only DLP, 4) CS + HTN, 5) CS + DLP, 6) DLP + HTN, 7) CS + HTN + DLP.

Participants in each level will be randomized into two study arms as follows.1Intervention (case) arm: Usual care + mHealth2Control arm: Usual care + paper-based recommendations and educational materials

In each level, participants will be assigned into two arms by block randomization with a 1:1 allocation using variable block sizes of 2, 4, 6, 8, and 10. Allocation of each subject to the study arms will be performed online to prevent selection bias and respect allocation sequence concealment (By concealing the allocation sequence). Allocation of each participant will be performed, just after inclusion and exclusion criteria are met and informed consent is signed by the participants. Computer-generated random number list will be utilized using permuted block stratified randomization. (Block stratified randomization Windows Version 6.0, by Steven Piantadosi, M. D., Ph.D., Cedars-Sinai Medical Center).

The practitioners who evaluate the risk factors controlling status are blinded to the group assignment.

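### The controlled-dyslipidemia rule applies 55 mg/dL to the size of the LDL-C fall instead of the level reached, so as written no patient with baseline LDL-C of 110 mg/dL or more can be scored controlled

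*Protocol article*

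**What the plan says.** In the protocol article, section 3.7 (Definitions) handles DLP in two adjacent bullets.

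- Uncontrolled DLP: "The related cut-off value for the serum level of target LDL-C is ≤ 55 mg/dL", followed by "Values more than the listed cut-off value are considered uncontrolled DLP". Here 55 mg/dL is a serum level. No upper limit on LDL-C is given for entry.
- Controlled DLP: "Lowering serum level of LDL-C by < 55 mg/dL and ≥50% reduction from baseline", at the 3- or 6-month visit and maintained at later visits. Here 55 mg/dL is attached to the amount of lowering.

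Section 3.6 (Study outcomes) relies on these bullets: "The definition of being controlled for each risk factor is presented in the “Definitions” section". The primary outcome counts controlled risk factors from none to three. Four of the listed secondary outcomes include DLP: DLP alone, smoking with DLP, hypertension with DLP, and all three together. The success rule for DLP is not restated in other words anywhere in the article.

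**The concern.** The two bullets use the same figure for different quantities: a level in the first, a change in the second. In the second, a ceiling on the fall in mg/dL is joined by *and* to a floor on the fall in per cent. The two conditions pull against each other, and above a certain baseline they cannot both be met.

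What is at stake is the scoring of one of the three components of the primary outcome. A programmer or outcome assessor who follows the text would record failures for patients whose LDL-C has more than halved and lies below 55 mg/dL. If the discrepancy is noticed only at analysis, choosing a reading becomes an endpoint decision taken with data in hand.

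**Working it through.** **Inputs.** All come from section 3.7: fall < 55 mg/dL and fall ≥ 50% of baseline (controlled bullet); target level ≤ 55 mg/dL, with higher values uncontrolled (uncontrolled bullet). Let B be baseline LDL-C, F the follow-up value and R = B − F the fall, in mg/dL.

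**The plan's own DLP figure.** The only calculated DLP figure is the 257 per arm in Table 3 (success 0.2 versus 0.3, power 80%, 10% loss). With pooled variance and no continuity correction,

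n = [z_α √(2 × 0.25 × 0.75) + z_β √(0.2 × 0.8 + 0.3 × 0.7)]² / 0.1².

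A one-sided 0.05 test gives 231, and 231 / 0.9 = 256.7, so 257 is reproduced. A two-sided test gives 294, and 294 / 0.9 = 326.7, i.e. 327. The calculation uses only the two assumed rates, so the wording of the success rule does not enter it. The point below does not depend on it.

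**Step 1: the rule as written.** Success needs R < 55 and R ≥ 0.5B. Together, 0.5B ≤ R < 55, hence B < 110. At B = 110 the fall would have to be at least 55 and also less than 55. Enumerating every integer baseline from 110 to 400 with every integer follow-up value from 0 to B finds no passing pair.

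**Step 2: below 110.** The follow-up values that pass are B − 55 < F ≤ B/2.

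| Baseline | Follow-up values that pass as written |
|---|---|
| 80 | above 25, up to 40 |
| 90 | above 35, up to 45 |
| 100 | above 45, up to 50 |
| 110 or more | none |

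The window is 55 − B/2 wide: 15 mg/dL at a baseline of 80, 5 mg/dL at 100, zero at 110.

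**Step 3: the attained-level reading.** Success needs F < 55 and R ≥ 0.5B. This can be met at every baseline: F ≤ B/2 when B is below 110, and F < 55 when B is 110 or more.

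| Baseline to follow-up | Fall | Fall % | As written | Attained level |
|---|---|---|---|---|
| 100 to 48 | 52 | 52.0 | controlled | controlled |
| 100 to 40 | 60 | 60.0 | not controlled | controlled |
| 110 to 54 | 56 | 50.9 | not controlled | controlled |
| 140 to 50 | 90 | 64.3 | not controlled | controlled |
| 150 to 50 | 100 | 66.7 | not controlled | controlled |

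**Step 4: direction of the error.** Anyone who passes as written has B < 110 and F ≤ B/2, so F < 55, and therefore also passes the attained-level reading. The reverse fails, as the table shows. The written rule can only remove successes; it never adds one. The ones removed are exactly those with a fall of 55 mg/dL or more.

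**The case against.** The strongest reply is that nobody intended this. The neighbouring bullet fixes 55 mg/dL as a serum level. The DLP module in section 3.5 compares the entered LDL-C value with a target. Controlled hypertension in section 3.7 is also an attained level. A ceiling on improvement makes little sense as a success criterion, and nothing in the article shows that the literal rule would be coded. All of this stands, and it makes *by* very likely a slip for *to*. It does not remove the point. The sentence defines an endpoint threshold, it is the only version given, and following it produces wrong scores.

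Three stronger readings are tempting, and the article does not support them.

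- *A given share of successes would be lost.* Any percentage needs a baseline LDL-C distribution and a distribution of change. The article gives neither, so simulated losses would only reflect the parameters chosen.
- *An app that produces larger falls would gain nothing, or would lose successes.* This is untrue in general. A patient at 100 who reaches 48 and not 60 becomes a success under the written rule too. Some large falls are scored as failures, but stronger response can still raise the written success rate.
- *The success rates would no longer match the 20% and 30% in Table 3.* Those rates are linked to a cited pooled analysis whose definition of control is not given. Whether they match even the attained-level rule is unknown, so a loss of match cannot be shown.

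**Conclusion.** The point holds as an error in an outcome definition, probably of wording. Two results follow from the text alone, without assumptions: no patient with baseline LDL-C of 110 mg/dL or more can be scored controlled, and below 110 a larger fall to a lower level can fail where a smaller one passes. If the rule were coded literally, true successes would be removed in both arms. Because those removed are the largest falls, a difference between arms in DLP control would be expected to shrink; this last step assumes that any benefit of the app acts through larger LDL-C falls. The number of patients affected cannot be computed from the article. Under the evident intended reading no estimate changes, and the sample size calculation is unaffected under either reading.

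**What to change.** In section 3.7, reword the controlled-DLP bullet so that 55 mg/dL is the level attained, in line with the target level in the bullet before it: *to a level of < 55 mg/dL* in place of *by < 55 mg/dL*. Code the DLP component of the primary count and of the four secondary outcomes from that wording, and record the correction before outcome data are seen. If the full protocol or analysis plan already states an attained level, confirm that the code follows it and correct the article.

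The cost is one wording change and a check of one line of code. No new measurements or patients are needed.

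The rewording does not settle two neighbouring questions in the same bullets, which the sponsor should reconcile separately. A value of exactly 55 mg/dL is neither uncontrolled (above 55) nor controlled (below 55). And a patient going from 80 to 50 is below the target level but fails the percentage condition, since 30/80 = 37.5%.

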### Design

2.3

This parallel-group single-blinded randomized controlled trial study, has been designed to compare the impact of 6 months using an mHealth application and paper-based educational content on risk factors control in CAD patients.

The study protocol is according to the Standard Protocol Items: Recommendations for Interventional Trials (SPIRIT) 2013 Statement [16].

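### The three risk factors summed in the primary count are scored on different clocks, and none of the definitions plainly yields the separate 3-month and 6-month statuses that the analysis uses

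*Protocol article*

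**What the plan says.** Section 3.6 (Study outcomes) defines the primary outcome as the number of controlled risk factors, from none to three, with "control measured at 3 and 6 months after randomization". It refers to section 3.7 (Definitions) for what controlled means, so section 3.7 is the scoring rule. It gives three different timings:

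- **HTN:** "Maintaining BP below the target treatment level (130/80 mmHg) at the time of office measurements", where an office measurement is the average of two readings on separate occasions, then "at the end of 3 and 6 months from randomization and/or during one-week daily home measurements (average of records) before clinic visits".
- **DLP:** LDL-C below the cut-off and reduced by at least half from baseline, "in any of the follow-up visits at the end of 3 and 6 months from randomization and remaining controlled in the next visits".
- **Smoking:** "Continuous abstinence in at least 4 weeks during 6 months following up".

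Section 3.12 (Statistical methods) compares the proportions controlled between arms by a separate chi-square test at baseline, month 3 and month 6. It then uses logistic regression to "determine the effect of the intervention on the control of risk factors at the end of 6 months". Section 2.3 (Design) states the aim as to "compare the impact of 6 months using an mHealth application" with paper-based education.

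**The concern.** A count from 0 to 3 is interpretable only if its components refer to the same moment. Here one component may require two visits, one may be met at either visit if it then persists, and one may be met in any four-week stretch. The same course of response can therefore add a point for one factor and none for another.

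The analysis needs a status at month 3 and a status at month 6. A definition that looks ahead to month 6 cannot give the first. A definition that looks back to month 3, or to any earlier window, does not give the second. If the wording stays open, the programmer must choose a reading of a component of the primary outcome, possibly after results are known. If the both-visits reading of HTN is chosen, BP control gained in the second half of a six-month intervention is not counted.

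**Working it through.** **1. The definitions set side by side.** Take a patient seen at both visits, with + for at target and − for not at target on that visit's own measurement. End-of-study scores are:

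| Month 3 | Month 6 | HTN, both-visits reading | HTN, each-visit reading (month 6) | DLP as written |
|---|---|---|---|---|
| − | − | not controlled | not controlled | not controlled |
| + | − | not controlled | not controlled | not controlled |
| − | + | **not controlled** | controlled | **controlled** |
| + | + | controlled | controlled | controlled |

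- In the third row, HTN under the both-visits reading and DLP part company. A patient with both factors and this course scores one point, not two.
- With both visits attended, the DLP rule gives the same answer as month-6 status. It does not give a month-3 status: the second row is at target at month 3, but the rule withholds success because control did not last.
- The both-visits reading of HTN gives neither a month-3 status (it needs the month-6 value) nor a month-6 status (third row).
- Smoking does not fit the table. Four weeks' abstinence early on, followed by relapse, meets the definition although the patient smokes at month 6. Abstinence that begins after month 3 also meets it and says nothing about month 3.

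**2. Which HTN reading does the text favour?** The DLP bullet uses the same reference to months 3 and 6 but adds wording that lets either visit count. The HTN bullet has no such wording and speaks of maintaining BP, which favours both visits. Sections 3.6, 3.8 and 3.12 treat months 3 and 6 as occasions on which status is determined, which favours each visit. No sentence settles it.

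**3. Office and home BP.** The definition joins the office and home criteria by "at the end of 3 and 6 months from randomization and/or during one-week daily home measurements (average of records) before clinic visits". Read as *or*, a home average can qualify a patient whose office BP is above target. Read as *and*, both are needed. The reference to clinic visits in the plural again does not say each or both.

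**4. Illustration of size (assumptions, not protocol facts).** The protocol gives no visit-level HTN rates. Table 3 gives 0.11 (control) and 0.165 (intervention) without saying to which definition they refer.

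*Stated figure first.* A two-proportion normal approximation with pooled variance, one-sided 5% and 80% power gives 484 per arm, and 484/0.9 = 538, as in Table 3. A two-sided test gives 615, and 684 after loss. Sidedness is a separate matter.

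*Both-visits rate.* Assume that Table 3's rates p are single-visit rates, equal at both visits, with within-patient correlation r:

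P(both) = p² + r·p(1−p)

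At r = 0.5: 0.0121 + 0.5 × 0.0979 = 0.061 for control, and 0.0272 + 0.5 × 0.1378 = 0.096 for intervention.

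Share of month-6 controlled patients who fail the both-visits rule: 1 − P(both)/p = (1−p)(1−r).

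| r | Control | Intervention | Difference | Share reclassified (control / intervention) | Power, 484 per arm, two-sided | One-sided |
|---|---|---|---|---|---|---|
| single visit | 11.0% | 16.5% | 5.5 points | – | 70% | 80% |
| 0.7 | 8.1% | 12.4% | 4.3 | 27% / 25% | 60% | 71% |
| 0.5 | 6.1% | 9.6% | 3.5 | 45% / 42% | 53% | 65% |
| 0.3 | 4.1% | 6.9% | 2.7 | 62% / 58% | 46% | 58% |

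These are figures for HTN alone, which is a secondary outcome. The effect on the 0–3 count is not computed.

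**The case against.** A reader might infer that HTN counts as controlled only if BP is below target at both visits, so that late BP responders are scored as failures. The protocol does not establish this. It nowhere says that both visits are required or that control first reached at month 6 fails. The phrase naming months 3 and 6 can simply list the scheduled visits, as it does in the DLP bullet, and the by-visit tests and the month-6 model fit scoring at each visit. The home-BP route may also let a patient qualify without office control at both visits. All of this stands, and it limits the point to ambiguity and misalignment.

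Nor is looking ahead peculiar to HTN: a month-3 DLP success also depends on the later value, and smoking has the loosest clock of the three.

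A reader might also infer that power falls from 70% to 46–60%. The arithmetic is right, but it rests on an unstated meaning of Table 3. If 11% and 16.5% already describe control as defined, there is no loss. The 70% starting point comes from applying a two-sided test to a size that reproduces one-sided. And 484 per arm is the HTN-only requirement less 10%, not the expected number of hypertensive patients. If Table 3's 0.47 applied to those enrolled (an assumption), there would be 772 × 0.47 ≈ 363 per arm before loss.

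Finally, sustained BP control is a legitimate and stricter endpoint. That is true, but it would then have to be stated, applied to all three factors alike, and matched by the analysis.

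**Conclusion.** The point holds as an inconsistency in the definition of the primary outcome. Section 3.7 puts the three summed factors on three clocks. The DLP rule gives no month-3 status, the smoking rule is tied to neither visit, and the HTN rule is open between both visits and each visit, and between office and home BP. Section 3.12 needs a status at each visit. Under one natural but not compelled reading of the HTN rule, a patient who first reaches both BP and LDL-C targets at month 6 is scored controlled for DLP and not for HTN.

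Its size cannot be fixed from the protocol. The 25% to 62% reclassification and the power figures illustrate what the choice of reading could do to the HTN component under the assumptions listed; they do not estimate a loss in this trial. The conclusion does not depend on them. This should be corrected before analysis.

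**What to change.** Before analysis, reword section 3.7 so that each factor is scored at month 3 and at month 6 from that visit's data only (with the baseline LDL-C for the percentage reduction). Use month-6 status in the 6-month primary count and month-3 status in the 3-month comparison. For smoking, state how the four weeks of abstinence relate to the visit, so that early abstinence followed by relapse is not carried into the month-6 status unnoticed. Report control sustained at both visits as a secondary outcome, for all three factors.

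For HTN, also replace the joint office and home criterion by one rule that applies at each visit and in both arms, stating whether office BP, home BP, either or both decides. This matters because the control arm records home BP on paper charts and the intervention arm in the app.

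The cost is rewording. No new data are needed, because Table 2 already schedules BP, smoking status and LDL-C at both visits. The downside is that the 6-month result no longer requires durable control; the secondary outcome covers that.
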